## Abstract

**Background:**

Pressure ulcers are a major problem, especially in nursing home patients, although they are regarded as preventable and there are many pressure relieving methods and materials. One such pressure relieving material is the recently developed Australian Medical Sheepskin, which has been shown in two randomized controlled trials [1,2] to be an effective intervention in the prevention of sacral pressure ulcers in hospital patients. However, the use of sheepskins has been debated and in general discouraged by most pressure ulcer working groups and pressure ulcer guidelines, but these debates were based on old forms of sheepskins. Furthermore, nothing is yet known about the (cost-)effectiveness of the Australian Medical sheepskin in nursing home patients.

The objective of this study is to assess the effects and costs of the use of the Australian Medical Sheepskin combined with usual care with regard to the prevention of sacral pressure ulcers in somatic nursing home patients, versus usual care only.

**Methods/Design:**

In a multi-centre randomised controlled trial 750 patients admitted for a primarily somatic reason to one of the five participating nursing homes, and not having pressure ulcers on the sacrum at admission, will be randomized to either usual care only or usual care plus the use of the Australian Medical Sheepskin as an overlay on the mattress.

Outcome measures are: incidence of sacral pressure ulcers in the first month after admission; sacrum pressure ulcer free days; costs; patient comfort; and ease of use. The skin of all the patients will be observed once a day from admission on for 30 days. Patient characteristics and pressure risk scores are assessed at admission and at day 30 after it.

Additional to the empirical phase, systematic reviews will be performed in order to obtain data for economic weighting and modelling.

The protocol is registered in the Controlled Trial Register as ISRCTN17553857.

## Background

"*How to prevent or heal pressure sores is an ever-present problem for nurses, and they have had many and varied ideas for solving it. Some of their methods have been helpful; others have been failures. Sometimes old methods that were not 100 per cent effective have been put aside for new ones, and, occasionally, an old one is revived to be tried again. Such a method is sheepskin therapy (Woodruff, **1952**) *[3]."

This historical quote is interesting, since it shows that pressure ulcers have been a major problem for many years. Furthermore it is interesting because it states that old therapies sometimes are revived, such as the sheepskin. More than 50 years later the sheepskin, now labelled as the 'Australian Medical Sheepskin', has its second revival.

Pressure ulcers are highly prevalent, especially among elderly residing in nursing homes, where about 30% of the patients are suffering from these sores [4-7]; a Canadian study in two nursing homes even found a prevalence rate up to 53% [8]. A USA-study in 12 nursing homes found a mean incidence rate of 13.6%, varying between 3 and 31% [9]. Incidence rates for Dutch nursing homes are scarce: one study found an incidence rate of 25% in the first four weeks after admission [10]. Pressure ulcers are not just a very common problem, they also represent a major burden and reduce quality of life for patients and their carers; pressure ulcers cause prolonged contact with the health care system, pain, discomfort and inconvenience [11-15].

Pressure ulcers are considered as a problem that to a large extent can be prevented by good care; therefore the incidence and prevalence rates are now put forward by many health care, professional and governmental organizations as an indicator of the quality of health care [16-20].

The prevention and therapy of pressure ulcers are very costly [13,21-25]. However, economic evaluations of pressure-relieving devices for the prevention of pressure ulcers are few and far between [26].

Pressure ulcers develop when capillary circulation is obstructed by prolonged pressure. Also shear and friction are contributing factors for the development of pressure ulcers. Therefore many interventions are in use to minimize pressure on bony prominences, such as repositioning and different kinds of pressure relieving devices [23,27,28]. Sheepskin is one such pressure relieving device. According to a literature review of the Australian Commonwealth Scientific and Industrial Research Organization (CSIRO) [29], it is known that sheepskins have pressure relieving properties, as was already demonstrated in studies dating back to the 1930s, 1950s and 1960s. Besides this, sheepskins have good moisture absorbing capacities. Therefore sheepskins have long been in use to prevent pressure ulcers. However, the old natural sheepskins could not retain their pressure reducing capacities after frequent washings; hygienic problems also arose because they could not withstand washing above 40 degrees. Later many attempts were made to produce artificial sheepskins, but none had the same pressure reducing or moisture absorbing properties. And so the use of sheepskins, both genuine and artificial, was almost completely discontinued and came to be regarded as ineffective [30]. Currently none of the guidelines known to us on pressure ulcer prevention and treatment mention or encourage the application of any form of sheepskin. However, in the 1990s, interest in genuine sheepskin was renewed. Marchand *et al.*[31] found promising results, which prompted the Australian Commonwealth Scientific and Industrial Research Organization, CSIRO, to develop new methods for producing new genuine medical sheepskins with very high pressure reducing capacities but without the disadvantages of the old sheepskins. The Australian Medical Sheepskin is a real genuine sheepskin, coming from the Australian Merino sheep. The sheepskin has a wool pile length of 30 mm, and a high density of wool piles. The sheepskin is tanned and processed in such a way that it has an increased resistance to urine and can withstand up to 60 washes at 80°C to achieve high-level thermal disinfection, without losing its moisture absorbing and pressure relieving properties.

This new Australian Medical Sheepskin has been tested extensively on pressure relieving characteristics, laundry procedures, disinfection, wear-and-tear, patient comfort and other aspects [32]. The necessary qualities for a sheepskin to be called an Australian Medical Sheepskin are described in the National Australian Standard AS 4480.1 [33]. The effectiveness of the Australian Medical Sheepskin in the prevention of pressure ulcers was first tested clinically in a randomized controlled trial in 297 elderly orthopedic hospitalized patients with very good results: incidence rate of pressure ulcers was 9.6% in the intervention versus 30% in the control group [1]. These results were confirmed in another randomized trial with 441 adults patients from different hospital wards [2]. Both studies were well designed, with the latter awarded for the best research article published in the Medical Journal of Australia of 2004. The application of Australian Medical Sheepskins is very easy for nursing and care personnel and for patients [1,2]. These trial results led to positive comments and recommendations in three recent systematic reviews [27,28,34].

However, the question arises as to whether these results in acute hospital patients can be replicated in the more chronic and vulnerable nursing home patients, who are generally at higher risk for developing pressure ulcers. In addition, in the Australian studies the cost-effectiveness was not assessed.

We therefore consider it is worthwhile to study the effects in nursing home patients and to assess the cost-effectiveness of the Australian Medical Sheepskin.

## Methods/Design

### Research aims and questions

The purpose of this study is to assess the costs and effects of the Australian Medical Sheepskin combined with usual care in the prevention of sacral pressure ulcers in nursing home patients, versus usual care only.

Research questions are:

1. What are the effects of the application of Australian Medical Sheepskins on the incidence rates of sacral pressure ulcers in somatic nursing home patients in the first month after admission compared to usual care?

2. What are the costs of the application of the Australian Medical Sheepskin?

3. What are the costs of the treatment for eventually developed pressure ulcers in the two study groups?

4. What is the cost-effectiveness of the Australian Medical Sheepskin compared to usual care?

5. What adverse effects do Australian Medical Sheepskins have?

6. How do patients and nursing and care personnel rate the (dis)comfort of Australian Medical Sheepskins and the ease of use of Australian Medical Sheepskins?

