### Outcomes

A distinction can be made between variables relating to the effectiveness (incidence, prevalence of pressure ulcers) and variables relating to costs (purchase and washing of the sheepskins on the one hand, and investment of time and materials cost for pressure ulcer treatment on the other). Both of these are necessary to compute cost-effectiveness.

The primary outcomes for this study are:

- the incidence of sacral pressure ulcers in the first 30 days after admissions,

- the costs of appliance of the sheepskin, and

- the costs related to treatment of the pressure ulcers that have developed.

Secondary outcomes are the presence of pressure ulcers on other places, quality of life, comfort of the sheepskin as experienced by the patients and ease of use of the sheepskin as experienced by the care personnel.

Influencing factors that will be measured are patient characteristics, the application of other pressure relieving interventions and materials and the use of incontinence materials.

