### Instruments

These outcomes, as well as influencing factors, will be measured by appropriate instruments, as far as possible we will use already existing and validated instruments. The EPUAP grading system is used to assess the presence and severity of pressure ulcers [38].

To this end a 'daily observation checklist' has been developed. Nurses use this checklist during the first 30 days after admission to report the presence/absence of sacral pressure ulcers, as well as the ulcer grade; the presence/absence of pressure ulcers on other locations and whether a sheepskin, repositioning, other support surfaces and incontinence material are applied.

When nurses feel uncertain about their observations they are instructed to call another specialized nurse, experienced in observing pressure ulcers.

Furthermore, a photographic series of the various pressure ulcer grades is available on each ward, as well as special glasses that can be used in order to differentiate better between blanchable and non-blanchable erythema. Finally, all nursing homes are offered a lesson in pressure ulcer observation.

The daily skin observations by nurses during routine care will be checked weekly by an experienced nurse observator from the nursing home itself and bimonthly by the principal investigator from the central research office.

Influencing patient factors that will be measured are age, gender, principal medical diagnosis category, surgery in the last month, presence of pressure ulcers at admission on other places than the sacrum, incontinence status, nutritional status (including body mass index), activity of daily living level (Barthel-index) and pressure ulcer risk score (Braden-scale). These are measured twice: at admission and at day 30 after it.

Furthermore the patients in the sheepskin group are asked at the end of the research period to rate the (dis)comfort of the sheepskin. For this purpose, a self-developed 7-item questionnaire with a 5-point rating answer structure was developed.

Data about costs that will be gathered are the costs of buying sheepskins, costs of washing sheepskins, costs of treatment of pressure ulcers (medication, wound care materials, diagnostics, kind of specialized consultants and time involved, and extra time for nurses/carers with regard to pressure ulcer treatment).

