For this purpose, invoices from the firms in question will be used, or the best approximations as far as these are available in Dutch (governmental) sites/organizations.

In summary, in order to register the above-mentioned data, the following five forms were created: admission form, daily observation form, end of research period form, sheepskin comfort questionnaire and the pressure ulcer therapy cost form (these forms in Dutch can be obtained on request from the first author).

The initial assessment at admission is completed for all patients that fulfill the inclusion criteria, in order to conduct a post hoc check as to whether there was selective attrition in patients not willing to participate.

Ease of use of the sheepskin for carers will be measured by group interviews to be held on three occasions during the research period.

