With regard to treatment adherence, patients from the intervention group are asked only to keep the sheepskin in their bed for 30 days. No other action is required from patients other than actions that are also asked in the control group. However it remains possible that some patients after a few days will refuse the sheepskin (e.g. because of itching, not feeling comfortable, too hot, or other reason): in these cases the use of the Australian Medical Sheepskin will be stopped without persuading patients to continue, but they will be asked if the daily skin observations can be continued. Records will be kept of patients that have discontinued the use of the Australian Medical Sheepskin (including reasons to stop), and they will be analyzed in the group they were randomized, according to intention to treat analysis principles.

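### Adverse effects are a stated research question, but no listed outcome, described form content or analysis covers them, and non-ulcer reactions have no record in the usual-care arm

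*Protocol article*

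**What the plan says.** Under Research aims and questions, the protocol article numbers six questions. The fifth is "What adverse effects do Australian Medical Sheepskins have". The sixth begins "How do patients and nursing and care personnel rate the (dis)comfort of Australian Medical Sheepskins" and goes on to ease of use, so the article treats harms and comfort as separate matters.

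Under Outcomes, the primary outcomes are "the incidence of sacral pressure ulcers in the first 30 days after admissions", the cost of using the sheepskin and the cost of treating ulcers that develop. On the rest it says: "Secondary outcomes are the presence of pressure ulcers on other places, quality of life, comfort of the sheepskin as experienced by the patients", followed by ease of use for care personnel.

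Under Instruments, nurses complete the daily checklist "to report the presence/absence of sacral pressure ulcers, as well as the ulcer grade". It also covers ulcers at other locations and "whether a sheepskin, repositioning, other support surfaces and incontinence material are applied". The section sums up the data collection by saying that "the following five forms were created: admission form, daily observation form, end of research period form, sheepskin comfort questionnaire" and a form for ulcer treatment costs.

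Data-analysis covers ulcer incidence and prevalence, ulcer-free days, time of onset and an economic model.

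Possible reactions are named only in the Discussion, in the paragraph on treatment adherence, where itching, discomfort and heat are examples of why a patient might refuse the sheepskin. There the article says "Records will be kept of patients that have discontinued the use of the Australian Medical Sheepskin (including reasons to stop".

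**The concern.** A research question needs an outcome, a way of recording it and an analysis. Question 5 has none of these in the article's own account. Two consequences follow for non-ulcer reactions.

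- **Ascertainment.** A record tied to stopping does not register a patient who itches or overheats but keeps the sheepskin.
- **Attribution.** Itching, heat and skin irritation can plausibly occur in nursing home patients without a sheepskin. With no matching record under usual care, the trial cannot separate what the sheepskin adds from what would have occurred anyway.

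The primary comparison is not affected. What is at stake is one of six stated questions, in a trial that already has every patient's skin observed daily for 30 days.

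**Working it through.** The article states no figure on this point, so there is none to reproduce. The check traces each question through the article's sections.

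**Step 1: questions against Outcomes.**
- Question 1 (sacral ulcer incidence): first primary outcome.
- Question 2 (cost of the sheepskin): second primary outcome.
- Question 3 (cost of treating ulcers): third primary outcome.
- Question 4 (cost-effectiveness): computed from the effect and cost variables, as Outcomes says.
- Question 5 (adverse effects): no entry.
- Question 6 (comfort and ease of use): two secondary outcomes.

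Five of the six questions have a counterpart; question 5 does not.

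**Step 2: question 5 against the data described.**
- Daily checklist: ulcers at the sacrum and elsewhere, and preventive measures in use. It is not limited to one arm and runs for 30 days. No non-ulcer reaction is listed.
- Comfort questionnaire: seven items, sheepskin group only, once at the end of the period. It serves question 6, and the items are not shown.
- Reasons for stopping: only patients who discontinue the sheepskin, hence sheepskin arm only.
- End-of-period form: not itemised. The article says only that patient factors are measured again at day 30.
- Carer group interviews: three occasions, on ease of use.

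For itching, heat or another skin reaction, this leaves one source that depends on stopping and one possible source at a single time point. Neither has a usual-care counterpart.

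**Step 3: question 5 against Data-analysis.** No summary or comparison of adverse effects appears.

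**Step 4: what recording in both arms would give.** The documents contain no reaction rates, so these pairs are assumptions chosen to span a range. With 375 per arm (Sample size calculation), the 95% half-width for a difference in proportions is 1.96 × sqrt[(p1(1−p1) + p2(1−p2))/375].
- 5% v 2%: sqrt[(0.0475 + 0.0196)/375] = 0.0134, so ±2.6 points.
- 15% v 5%: sqrt[(0.1275 + 0.0475)/375] = 0.0216, so ±4.2 points.
- 30% v 20%: sqrt[(0.21 + 0.16)/375] = 0.0314, so ±6.2 points.

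These show the precision available after the change. They say nothing about how large an under-count the present plan would produce.

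**The case against.** The strongest case on the other side has four parts.

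1. **The forms are not shown.** They are available on request, the end-of-period form is not itemised, and an article may leave form content to a fuller document. This stands as a limit: a reader might infer that adverse effects are not collected at all, and the article does not show that. It does not remove the mismatch, because the article states the question and then sets out outcomes, form contents and analyses without it.
2. **There are sources other than patients who stop.** The comfort questionnaire goes to the sheepskin group generally and may ask about itch or heat. Ulcers elsewhere are recorded daily without limit to one arm, carers are interviewed, and patients who stop are asked whether skin observation can continue. This also stands. A reader might infer that the answer would rest on stoppers alone, or that the trial will report an adverse-effect rate counted from them. The questionnaire contradicts the first, and the article nowhere promises the second.
3. **Question 5 does not ask for a comparison.** Questions 1 and 4 refer to usual care and question 3 to both study groups; question 5 does not. A descriptive list in exposed patients could answer it as worded, so the missing comparator contradicts no promise. It is still a weakness: without it, a listed complaint cannot be attributed to the sheepskin.
4. **Subjective complaints recorded by unblinded nurses may be biased.** This is true and has to be stated with the result. It applies equally to the one-arm records now described.

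**Conclusion.** The point holds in a limited form. Question 5 is not linked to any listed outcome, described form content or analysis. As described, the plan gives no between-arm record of non-ulcer reactions, and it may miss those in patients who keep the sheepskin.

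The documents do not let the under-count be sized. Any figure for it would only restate an assumed share of reacting patients who stop, and would further assume that the questionnaire picks up nothing. The conclusion rests on the contents that the article lists; an unlisted item on the end-of-period form or the questionnaire would narrow the gap. The change should be made, but the primary outcome does not depend on it.

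**What to change.** - Name adverse effects as a secondary (safety) outcome under Outcomes, and state which instrument answers question 5.
- Add items for itching, feeling too hot and other skin reaction to the existing daily observation form. Complete them in both arms, whether or not the sheepskin is still in use.
- Under Data-analysis, report the proportion of patients with at least one event by randomised arm, and the difference with a 95% CI. Report reasons for stopping separately.
- If the end-of-period form or the comfort questionnaire already holds relevant items, say so.

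The cost is a few tick-boxes on a form nurses already complete each day, and one table. Inclusion began on 1 May 2007, so patients already enrolled will lack the items; the table should give the number observed in each arm. Nurses and patients know the allocation, so reporting bias should be stated as a limitation of the comparison.

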### Design

The proposed study concerns a prospective multi-centre randomised controlled trial with one experimental and one control group. The starting point is a superiority design with the research hypothesis that Australian Medical Sheepskins are a better pressure relieving device than usual care; that they will reduce the incidence rates of sacral pressure ulcers; and will also reduce costs involving pressure ulcer treatment.

Data will be gathered primarily in an empirical way and additionally through systematic literature searches with regard to the cost-effectiveness question.

For assessing the cost-effectiveness, the Australian Medical Sheepskin will be compared only to usual care and not to other pressure relieving materials. The perspective of the health care organisation will be considered to measure the cost-effectiveness.

### Participants

The study population will concern patients newly admitted for a primarily somatic condition to one of the five participating nursing homes. Only patients who are free of sacral pressure ulcers on admission will be included. Further inclusion criteria are: adult; not having darkly pigmented skin (because of difficulty in diagnosing grade 1 pressure ulcer); having an expected stay of more than one week; and consenting to the research.

For practical reasons and because 74% of nursing home patients in the Netherlands are at risk for pressure ulcer development [4], we have chosen to involve all patients, and not only patients at risk.

The patients will be recruited from 5 different Dutch nursing home care groups (Amstelring, Florence, Frankeland, Sutfene, Swinhove) involving seven different geographical locations and 18 wards. The selection of the nursing homes was made on the basis of the customer list of the laundry company that we contacted, and which is able to do the washing and drying of the sheepskin, according to the Australian Standard [35].

Inclusion of patients started on May 1^st ^2007 and will proceed until the targeted number of patients is reached, for a maximum of 1.5 years. It is expected that enough patients will be admitted during this period to reach the necessary number as was calculated by power-analysis.

